
### Sample size

To detect a between-group difference in the TIL Scale of 2.2, with 90% power and 0.05 (two-sided) significance level, a total of 106 patients are required. Calculations were based on the anticipated mean of 8.2 and standard deviation 3.2 of the novel TIL in TBI patients admitted to the ICU [38]. The patient group treated with C1-INH is estimated to have an average TIL of 6 [39, 51]. Both treatment groups will include 53 patients to power the trial and to account for withdrawal and loss to follow-up (approximately 10%). With this sample size, a difference of 2.2 on the TIL scale can be detected, which is clinically relevant as it corresponds to one medium level of intervention (such as CSF drainage or mannitol treatment) less to control ICP indicating a significant treatment effect. As no minimal clinically important difference (MCID) for the TIL scale is defined in the literature, we will adhere to this shift of 2.2 points on the right-skewed scale.

### Statistical analysis

The trial profile will be summarized using a Consolidated Standards of Reporting Trials (CONSORT) flow diagram, including the reasons for non-eligibility and non-enrollment [52]. The data will be analyzed on an intention-to-treat basis with all randomized patients included in the analysis. Baseline variables will be summarized using descriptive statistics. In line with the IMPACT recommendations, the investigators plan to analyze the primary outcome TIL by using a linear model with covariate adjustment for age, GCS, and pupillary reactivity to adjust for baseline imbalances and to optimize statistical efficiency [53]. TIL will be analyzed as the TILmax for each patient, and the median for each group will be calculated. The treatment effect estimated will be based on the adjusted mean differences including 95% confidence intervals. To maintain the 5% familywise error rate, while still comparing the multiple clinically relevant endpoints, we will use a serial gatekeeping approach for statistical testing [54]. Analysis of GOSE at 6 months, as an ordinal outcome, will be done only if a significant difference in TIL is found. The co-primary endpoint GOSE will not primarily be used to declare the study success. For the analysis of GOSE at 6 months, covariate adjustment for the strongest predictors of outcome in TBI will be performed as mentioned above. The effect estimate will be an adjusted proportional odds ratio with 95% confidence interval for the shift in the direction of a better outcome on the GOSE. The ordinal regression model assumes that the odds ratio for each potential cut of the GOSE is constant no matter which cutoff point is taken (proportional odds assumption). Although the common odds ratio is formally only valid if the proportional odds assumption is met, the common odds ratio can be interpreted as a summary measure of treatment effect, even if the odds ratios differ by cutoff [55, 56]. In this study, the resulting single, common odds ratio can be interpreted as the average shift over the GOSE scale at 6 months caused by C1-INH compared to placebo [56].

Secondary analyses will be compared between the treatment groups using unadjusted and adjusted (ordinal) logistic and linear regression. Time-to-event analyses will be undertaken using Kaplan-Meier curves, as well as Cox proportional hazards regression models.

Subgroup analyses on primary outcomes will be performed in the following subgroups: age (< 65 or ≥ 65 years), GCS on admission (moderate and severe TBI), and ICP-directed treatments (high intensity vs. low intensity, secondary DC vs. no secondary DC), and will be presented in forest plots.

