## Methods

### Trial design

Complement inhibition: Attacking Overshooting inflammation @fter Traumatic Brain Injury (CIAO@TBI) is a multicenter, randomized, blinded, placebo-controlled, phase II trial in patients with TBI. The protocol is designed in accordance with the Standard Protocol Items: Recommendation for Interventional Trials (SPIRIT) 2013 Checklist (Additional file 1) [32]. Patients will be recruited in three-level one trauma centers, including the coordinating neurotrauma research unit of University Neurosurgical Center Holland seated at Leiden University Medical Center (LUMC) and Haaglanden Medical Center (HMC) in close collaboration with Erasmus Medical Center Rotterdam (EMC) and Amsterdam University Medical Centers, location AMC. Patients will be randomized at the ICU in the first 12 h after trauma to receive (1) one dose of C1-INH 6000 IU intravenously (IV) or (2) one placebo injection with 0.9% saline IV.

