### Randomization

Patients in the trial are allocated to treatment with C1-INH or placebo in a 1:1 ratio, via a confidential interactive web-based algorithm software (Castor EDC, Ciwit B.V., Amsterdam, The Netherlands) using permuted block sized with stratification by study center. Randomization will be performed by the treating neurosurgeon, neurosurgical resident, or research physician after obtaining informed/deferred consent. An automatically generated email will be sent to the pharmacy with information regarding treatment allocation after randomization through Castor EDC.

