### Trial interventions

The intervention is the IV administration of C1-INH compared to a placebo (0.9% saline). A single dose of 6000 IU will be administered within 12 h after trauma. Blood samples (2 EDTA, 1 serum, and 1 citrate tube) will be drawn from both patient groups before administration and at 6, 12, 24, 48, 72, and 96 h after administration of C1-INH or placebo in the ICU. Moreover, if an external venticular drain (EVD) is placed as part of standard care to reduce CSF pressure, additional liquor samples will be drawn before administration and 24, 48, 72, and 96 h after administration of C1-INH or placebo in the ICU. All samples will be centrifuged and aliquoted in 500 μl samples as quickly as possible and afterwards stored at − 80 °C. Other interventions are unaltered from local treatment protocols and will include standard of care in both groups. This might include concomitant therapies, such as a decompressive craniectomy. During hospitalization, patients are closely monitored for (serious) adverse events (SAEs). Moreover, health-related questionnaires will be filled out by the patients or proxies at discharge and at 3 months, 6 months, and 12 months after head trauma. A flowchart of the study design is shown in Fig. 2. All study procedures will be performed according to the designated study operating procedures (SOPs).

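### Randomisation is stratified by study centre, but the named TIL and GOSE models leave centre out; if centre is prognostic, the TIL test is conservative and a little power is forgone

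*Protocol article*

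**What the plan says.** The Randomization section has patients "allocated to treatment with C1-INH or placebo in a 1:1 ratio", "using permuted block sized with stratification by study center". Centre is the only stratification factor named.

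The Statistical analysis section specifies the primary TIL analysis as a "linear model with covariate adjustment for age, GCS, and pupillary reactivity" and gives the purpose of the adjustment: "to adjust for baseline imbalances and to optimize statistical efficiency". For GOSE at 6 months it says that "covariate adjustment for the strongest predictors of outcome in TBI will be performed as mentioned above", and that "The effect estimate will be an adjusted proportional odds ratio with 95% confidence interval". Centre is in neither model, as a fixed or a random effect, and no other section adds it.

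The Trial interventions section says: "Other interventions are unaltered from local treatment protocols". The Trial design section says "Patients will be recruited in three-level one trauma centers" and then names four hospitals, so the number of strata is three or four.

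**The concern.** Blocks within centre keep the arms nearly balanced on centre, so differences between centres contribute little to the true sampling variance of the treatment effect. A model without centre still counts those differences as residual noise. If centre predicts the outcome, the reported standard error then exceeds the true one.

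TIL is exposed to this because it scores what the treating team does to control ICP, and the endpoint is each patient's highest daily score. With care left to local protocols, two centres could give different scores to similar patients. GOSE is tested only if TIL is significant, so conservatism on TIL also reduces the chance of reaching GOSE. The stated covariate list thus omits the one variable the design balanced, although efficiency is one of its declared aims.

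**Working it through.** **Inputs from the article (Sample size).** TIL difference 2.2, SD 3.2, two-sided alpha 0.05, power 90%, 53 per arm, loss about 10%.

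**Assumed.** The share of TIL variance lying between centres (ICC), taken as 0 to 0.20. Three or four centres of equal size. Age, GCS and pupils are left out of the arithmetic.

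**Reproducing the plan's figure.** n per arm = 2 × (3.2/2.2)² × (1.960 + 1.282)² = 44.5, so 45. The t-test version needs 46 (power 90.4%). 46/0.9 = 51.1, so 52 per arm and 104 in total. Allowing for a Wilcoxon efficiency of 0.955 gives 45/0.955 = 47.1, so 48; 48 × 1.1 = 52.8, so 53 per arm and 106 in total. The stated 106 is reproduced to within 2 patients by the t-test and exactly with the Wilcoxon allowance.

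**TIL.** After 10% loss about 48 per arm are analysed. Let b = 3.2 × √(2/48) = 0.653.
- True SE under centre-stratified blocks: b × √(1 − ICC).
- SE reported without centre: b × √(1 − ICC + f × ICC). Here f = (C − 1)/C is the average share of the between-centre variance that appears among C centres: 2/3 for three, 3/4 for four. f = 1 is an upper case.
- r = reported SE / true SE.
- Type I error without centre: 2 × [1 − Φ(1.96 × r)].
- Power without centre: Φ[(2.2 − 1.96 × reported SE)/true SE]. Power with centre: Φ[2.2/true SE − 1.96].

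Example, ICC 0.20 and four centres: true SE = 0.653 × √0.80 = 0.584; reported SE = 0.653 × √0.95 = 0.637; r = 1.09; type I error 3.3%.

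| ICC | r (f = 2/3, 3/4, 1) | Type I error, % | Power lost by omitting centre, points |
|---|---|---|---|
| 0 | 1.000 | 5.0 | 0 |
| 0.05 | 1.017, 1.020, 1.026 | 4.6, 4.6, 4.4 | 0.5, 0.5, 0.7 |
| 0.10 | 1.036, 1.041, 1.054 | 4.2, 4.1, 3.9 | 0.9, 1.0, 1.3 |
| 0.20 | 1.080, 1.090, 1.118 | 3.4, 3.3, 2.8 | 1.4, 1.6, 2.2 |

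In the upper case (f = 1), power without centre is 92.6%, 93.1% and 94.2% at ICC 0.05, 0.10 and 0.20. With centre it is 93.3%, 94.4% and 96.5%. At ICC 0 both are 92.0%.

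Simulation with 96 analysed, three or four centres and an assumed block size of 4 agrees. The reported SE is about 2%, 4% and 8–9% too large, and type I error is about 4.4–4.5%, 3.8–4.5% and 3.2–3.5%.

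**What SD 3.2 means.** The article presents it as the SD of TIL among TBI patients in the ICU, so it is read here as a total SD. If it were purely within-centre, power without centre would be Φ[(2.2 − 1.96 × 0.653 × r)/0.653]. At ICC 0.20 with four centres that is 89.1%, against 92.0% with centre.

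**GOSE.** The article states no effect size for GOSE. Proportional-odds fits were simulated with 96 analysed, an assumed odds ratio of 2.5 and an assumed GOSE distribution (2,500 trials per setting, Monte Carlo SE of power about 0.9 points).

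| SD of centre effects (log-odds) | Power without centre | Power with centre |
|---|---|---|
| 0.4 | 0.70–0.71 | 0.73–0.74 |
| 0.6 | 0.66 | 0.71–0.72 |
| 0.9 | 0.60 | 0.71–0.72 |

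At SD 0.6 the mean log odds ratio is 0.87 without centre and about 0.95 with it. The reported SE is 0.37 without centre and 0.38 with it, so the adjusted SE is not smaller. Without centre, that 0.37 exceeds the true sampling SD of 0.35, and type I error is 3.0–3.7%. With three centres and SD 0.9 the adjusted test rejected 6.6% of the time under the null, so part of that apparent gain is small-sample liberality.

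**The case against.** The strongest reply is that the harm is conditional. No section reports a between-centre variance. Care under local protocols makes a centre effect plausible but does not show that it is strong, and at an ICC of 0 there is no loss. That stands, and the point is worded accordingly.

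A reader might infer that the trial is underpowered for TIL. The documents do not support this: on the article's own inputs, with 3.2 as a total SD, power without centre is at least 92% at 48 per arm.

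A reader might also square the SE ratio for four centres (1.04, 1.08, 1.19) and conclude that about 4%, 8% or 19% of the sample is wasted. That treats an inflated reported SE as a real loss of precision. Stratified blocks have already lowered the estimator's true variance. Matching power between the two models puts the equivalent sample at about 2%, 4.5% and 9% with four centres, or 3%, 6% and 12% in the upper case.

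The linear-model argument does not carry over whole to GOSE, where part of the loss is the common odds ratio moving toward 1. The article also says GOSE is not the main basis for declaring success.

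Finally, an unseen SAP could add centre. That is possible, but the article does not leave the covariates open. It lists them, so a SAP that added centre would depart from the published list.

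**Conclusion.** The point holds in conditional form. The stratification factor is absent from both named models. If centre is prognostic, the TIL estimate remains unbiased and type I error is not inflated, but the reported standard error and interval are too wide and the test is conservative. For an assumed ICC of 0.05 to 0.20, the SE is about 2–9% too large, type I error is about 4.5% down to 3.2%, and TIL power is about 1–2 points below that of a model with centre. It stays above the planned 90% provided that 3.2 is a total SD.

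For GOSE the direction is the same, but the size rests on an assumed odds ratio, outcome distribution and centre SD. This is a missed efficiency gain that should be taken up, not a threat to the validity of the trial.

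**What to change.** Add study centre as a fixed effect to the linear TIL model and the proportional-odds GOSE model, alongside age, GCS and pupillary reactivity. Use the strata exactly as coded in the randomisation system, and state whether there are three or four. Make the change before unblinding. It costs 2 to 3 degrees of freedom and one line of wording, with no new data or patients.

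State also that the GOSE odds ratio is then conditional on centre.

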### Trial population and eligibility

All TBI patients presenting to participating hospitals are potentially eligible for this trial. The inclusion criteria are (1) age > 18 years, (2) clinical diagnosis of TBI with GCS < 13 on admission (with visible intracranial pathology on CT), and (3) invasive intracranial pressure monitoring by intra-parenchymatous transducer or ventricular catheter placement and management of increased ICP for at least 24 h. The exclusion criteria are (1) a clear, non-traumatic cause of low GCS on admission (e.g., toxic or cardiac cause); (2) not expected to survive more than 24 h after admission with the decision to abstain from aggressive treatment and induce palliative care; (3) brain death on arrival in the participating centers; (4) severe pre-trauma disability, defined as being dependent on other people; (5) known prior history of sensitivity to blood products or C1-INH; (6) patients with a history of hereditary angioedema (if known at admission); (7) patients with a history of thrombosis (deep vein thrombosis, cerebral venous sinus thrombosis, or pulmonary embolism) (if known at admission); and (8) patients that are pregnant (if known at admission).

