### Primary endpoints

#### Efficacy: Therapy Intensity Level (TIL) Scale

To measure the direct effect on the mechanism of action of C1-INH, our primary endpoint focuses on a decrease in ICP. ICP has been used as a surrogate endpoint for inflammation and testing of neuroprotective agents in many prematurely halted or failed clinical trials [37]. This might be due to the fact that ICP is an early surrogate marker during TBI but confounded by the modern neuro-ICU practices through escalating interventions (such as decompressive craniectomies (DC)) to immediately mitigate surges in ICP resulting in reduction of its sensitivity, as representing “severity of disease.” Therefore, this trial will focus on the intensity of ICP-targeted therapy based on the Therapy Intensity Level (TIL) Scale [38, 39]. The TIL Scale is designed to integrate all known and relevant ICP directed treatments into a single-summary score and was developed as part of the Interagency Common Data Elements scheme [38]. Since its introduction, the novel TIL Scale has been widely used in neurotrauma research, with excellent inter- and intra-rater reliability with minimal measurement errors [39]. The TIL Scale includes eight ICP treatment modalities each with a certain numerical score. Added together, TIL ranges between 0 and 38 points with a right-skewed distribution. Specifically, TBI patients admitted to the ICU have an average TIL score of 8.2 (SD 3.2), while general trauma patients on the ICU have a score of 2.2 (SD 0.9) [39]. The daily score will be calculated based on the highest score in each item per day (TIL24), to provide a metric on the maximal therapeutic intensity for ICP management for that day. The TIL score will be based on the highest TIL24 during the days an ICP monitor is in place (TILmax) and will be scored by a trained research team, and according to an SOP, thereby optimizing inter- and interrater reliability.

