### Ethics

The study protocol was designed in accordance with the ethical principles in the Declaration of Helsinki and the regional regulations, and the principles of Good Clinical Practice. Participants will be assessed for eligibility by the neurosurgical resident or research physician when an ICP monitor is placed within 12 h from trauma. Within this time frame, informed consent must also be obtained. Ideally, the treating physician will obtain informed consent from the patient. As the enrolled subjects will lack capacity to consent due to their level of consciousness at presentation, informed consent can be obtained within 12 h after trauma by a legally authorized representative of the patient. As TBI mostly occurs outside the domestic situation, family members are rarely available during the first hours after trauma [57]. Therefore, the treating physician will take responsibility for including the patient using “deferred proxy consent” if the following condition are met and documented: (1) the patients is in a potentially life-threatening situation and (2) the patient meets the eligibility criteria for trial entry. As there is a potential benefit with the administration of C1-INH and an urgent therapeutic timeframe of 12 h, deferred consent is justified in these patients [58–60]. Following enrollment via deferred consent, informed consent should still be obtained by a legal representative within 7 days after admission. Furthermore, the patient must agree to further participate in the study when mental capacity is regained. When consent for study continuation is provided, already collected data can be used. When study continuation is refused, already collected data can still be used when patients and/or proxies do not use their right to refuse this. Patients or proxies should always be informed about their right to refuse the use of obtained data. A team of dedicated research nurses and physicians are trained to perform the specific informed consent and randomization procedures. Moreover, a 24/7 study consultation telephone number can be reached to help with problems or questions during the study.

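### The primary TIL model adjusts for age, GCS and pupils but not for pre-dose ICP, so precision that is probably available at almost no cost is forgone; the analysis is valid and planned power is met without it

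*Protocol article*

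**What the plan says.** **Model.** Under Statistical analysis, the protocol article commits to a "linear model with covariate adjustment for age, GCS, and pupillary reactivity to adjust for baseline imbalances and to optimize statistical efficiency", citing the IMPACT recommendations. The list is closed and its purpose is stated. For GOSE at 6 months the same section says that "covariate adjustment for the strongest predictors of outcome in TBI will be performed as mentioned above", so one covariate set serves both efficacy endpoints.

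**Endpoint.** Under Efficacy: Therapy Intensity Level (TIL) Scale, "this trial will focus on the intensity of ICP-targeted therapy based on the Therapy Intensity Level (TIL) Scale". The analysed value is TILmax, the highest daily score while an ICP monitor is in place.

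**Availability of ICP.** Trial population and eligibility requires "invasive intracranial pressure monitoring by intra-parenchymatous transducer or ventricular catheter placement". Under Ethics, "Participants will be assessed for eligibility by the neurosurgical resident or research physician when an ICP monitor is placed within 12 h from trauma". Secondary endpoints includes an ICP burden measure calculated over the monitoring period.

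**Sample size.** "To detect a between-group difference in the TIL Scale of 2.2, with 90% power" and a "0.05 (two-sided) significance level, a total of 106 patients are required". The inputs are an "anticipated mean of 8.2 and standard deviation 3.2 of the novel TIL in TBI patients admitted to the ICU" and a treated mean of 6, with 53 per arm allowing for about 10% loss. No reduction of the SD for covariates is stated.

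**The concern.** The covariates are justified as predictors of clinical outcome after TBI, whereas TIL is a measure of treatment given in response to raised ICP. The article gives no reason why the best predictors of the first should also be the best predictors of the second. ICP before dosing is the obvious candidate for TIL, and the trial's entry conditions mean that it should exist for nearly everyone.

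If pre-dose ICP predicts TILmax beyond age, GCS and pupils, leaving it out has two effects. The variance it explains stays in the residual, so the confidence interval is wider than it need be. A chance imbalance in initial ICP also stays in the estimate, although adjusting for baseline imbalance is one of the model's two stated aims. Because GOSE is tested only if TIL is significant, precision on TIL bears on both efficacy endpoints.

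**Working it through.** **1. Inputs from the protocol article (Sample size).** Difference 2.2 (8.2 minus 6); SD 3.2; two-sided alpha 0.05; power 90%; 53 per arm including about 10% loss. Evaluable per arm: 53 × 0.90 = 47.7, taken as 48.

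**2. Reproducing the stated 106.** For a two-sample t-test without covariates (noncentral t), 45 per arm gives 89.7% power and 46 per arm gives 90.4%, so 46 are needed. Allowing for 10% loss, 46/0.90 = 51.1, rounded up to 52 per arm, or 104 in total. This is within 2 patients of 106. The plan's figure therefore rests on the SD of 3.2 with no covariate credit.

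**3. Power without pre-dose ICP and without credit for any covariate.** The noncentrality is 2.2 / (3.2 × √(2/n)).
- n = 48 per arm: 2.2 / (3.2 × 0.2041) = 3.37; power 91.5%.
- n = 53 per arm: 2.2 / (3.2 × 0.1943) = 3.54; power 93.9%.

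The 90% target is met in both cases.

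**4. Possible gain from pre-dose ICP.** The documents give neither the variance explained by the three covariates nor the correlation of ICP with TIL. Both are assumptions here: the three covariates explain 10%, and pre-dose ICP explains a share r² of the remainder, from 5% to 30%.

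Residual SD = 3.2 × √(0.90 × (1 − r²)). The 95% CI half-width at 48 per arm = t × residual SD × √(2/48), with t = 1.986 (94 degrees of freedom).

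| r² (assumed) | Residual SD | CI half-width | Power at 2.2 |
|---|---|---|---|
| 0 (model as written) | 3.04 | 1.23 | 94.0% |
| 0.05 | 2.96 | 1.20 | 95.0% |
| 0.10 | 2.88 | 1.17 | 95.9% |
| 0.20 | 2.71 | 1.10 | 97.6% |
| 0.30 | 2.54 | 1.03 | 98.7% |

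The narrowing is 1 − √(1 − r²): 2.5% at r² = 0.05 and 16% at r² = 0.30.

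**5. Cost if pre-dose ICP predicts nothing.** One degree of freedom. With treatment and three single-term covariates the residual degrees of freedom at 48 per arm are 91; with ICP added they are 90. The t quantile moves from 1.9864 to 1.9867, which is negligible.

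**The case against.** **Nothing is wrong with the model as written.** It prespecifies three baseline covariates under a named recommendation. Omitting another prognostic variable neither biases a randomised comparison nor inflates type I error, and almost any trial could be told to add one more. This stands. The point survives only because the article fixes a closed list, states efficiency as its aim, and omits the covariate closest to the endpoint.

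**Planned power is not lost.** A reader might infer that leaving out ICP makes the trial underpowered. The documents do not support that: the sample size takes no covariate credit and the 90% is reached without any. At 2.2 points the model as written is already near 94% under the assumption above, so there is little power left to gain at the planned effect.

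**ICP may predict TILmax only weakly.** The TIL section says that ICP is confounded by escalating treatment and loses sensitivity as a marker of severity. A pre-dose reading may already be a treated one. TILmax is a maximum over all monitored days, and the Background places oedema mostly around the third day. All this argues for the lower end of the assumed range. It does not make the covariate invalid: the reading precedes the infusion, so the study drug cannot have affected it. The article's caveat concerns ICP as an endpoint.

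**Availability is inferred.** A reader might take it as stated that every patient has a recorded pre-dose ICP. The text shows a monitor in place at eligibility assessment but names no such baseline variable, and the schedule figure is not shown. The inference is strong but remains an inference.

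**Conclusion.** The point holds as a low-cost improvement to the primary analysis, and no further. The covariate set for TIL is the one justified for clinical outcome, and it omits a baseline value that is close to the endpoint and should be obtainable for nearly all patients. The analysis is valid and unbiased, and meets its stated power.

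The size of what is forgone rests on assumed variance shares: about 0.03 points of CI half-width at the low end (1.23 to 1.20) and 0.20 at the high end (1.23 to 1.03), with 48 evaluable per arm. For the reasons given about early, possibly treated ICP, the true gain may lie near the low end or below it. The case for acting is that the cost is close to nil and that the covariate is credible only if fixed before results are seen.

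**What to change.** In Statistical analysis, prespecify the primary TIL model as treatment + age + GCS + pupillary reactivity + pre-dose ICP. Define pre-dose ICP once, as the last ICP recorded before the start of the infusion, entered as a continuous covariate. Handle missing values through the multiple imputation already planned for baseline data under Missing data. Confirm that the value is captured in the database. Make the change before unblinding.

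The cost is one sentence, one derived variable and about one degree of freedom. No patients or procedures are added, and the sample size calculation need not change.

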#### Efficacy: GOSE at 6 months

The co-primary efficacy endpoint will be the Extended Glasgow Outcome Scale (GOSE) at 6 months after trauma [40]. The GOSE [41], derived from its precursor the GOS [42], defines disability on an 8-point scale and incorporates emotional and cognitive disturbances affecting disability. A score of 5 or more indicates functional independence. The GOSE is designed as a structured interview and can also be applied through telephone [43] and e-mail or postal [44]. Two research nurses or researchers will independently grade the outcomes based on the GOSE in each patient according to the standardized approach. Disagreements will be resolved by consensus between them or by consultation of a third, independent investigator.

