### Secondary endpoints

Secondary endpoints include all-cause mortality rate during the study period (proportion), ICP burden (pressure and time dose (PTD) calculated as the area under the curve above ICP threshold of 20 mmHg) during ICP monitoring, occurrence of CT midline shift during hospitalization (proportion), ICU and hospital length of stay (median), and hospital discharge location (proportion). Additionally, the GOSE will be assessed at discharge and 3 and 12 months follow-up. Quality of life will be assessed using the Quality of Life after Brain Injury Scale (QoLiBri) [45, 46]. The QoLiBri is the first TBI disease-specific quality of life outcome tool that is cross-culturally developed and validated in large populations. This questionnaire consists of 37 items designed to assess the health-related quality of life (HRQol) after TBI, and the median score will be compared at 3, 6, and 12 months after trauma. To assess health and well-being, the Short Form (SF)-36 [47] and 5-Level EuroQol 5-Dimensional Questionnaire (EQ-5D-5L) will be assessed [48]. SF-36 is a subjective measure of health and well-being, and the median score will be compared at 6 and 12 months after head trauma. The EQ-5D-5L is a 5-dimensional generic instrument assessing health-related quality of life and health status and generates an index of health. This questionnaire will be filled out by patients at 6 and 12 months follow-up, and the median score will be compared between the groups. The cost-effectiveness of the C1-INH will be analyzed with the median costs per quality-of-life year (QALY), based on the iMTA Productivity Cost Questionnaire (iPCQ) and iMTA Medical Consumption Questionnaire (iMCQ) at 3, 6, and 12 month follow-up [49]. Blood and CSF samples will be used (up to 96 h after C1-INH administration) to measure complement activation in an exploratory fashion, using WIESLAB, C4b/C, C3b/C, and C5b-9 ELISA assays. Neurological damage will be analyzed with glial fibrillary acidic protein (GFAP) and ubiquitin C-terminal hydrolase-L1 (UCHL-1) biomarkers. To explore the interactions of the complement system with the coagulation cascade, routinely, PT, aPPT, PLT, d-dimer, and fibrinogen tests will be performed and compared between the treatment groups. The Disseminated Intravascular Coagulation (DIC) Score will be calculated for all patients as proposed by the Scientific and Standardisation Committee of the International Society on Thrombosis and Haemostasis [50]. Lastly, general inflammatory markers, TNF-alpha, and interleukins will be analyzed to explore the effect of C1-INH on neuroinflammation.

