### Reporting and dissemination

Reporting of our study will follow the CONSORT guidelines [52]. The results of this study will be presented at national and international scientific conferences and will be published in peer-reviewed journals without any publication restrictions. All authors who fulfil the authorship criteria will be included in future publications. There is no intended use of professional medical writers. Furthermore, the results of the current trial will inform a phase III clinical trial with a large and pragmatic enrollment rate powered solely on efficacy regarding clinical outcome improvement.

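### The plan gates the analysis of 6-month GOSE, not only its confirmatory test, on a significant TIL result, so a co-primary endpoint may get no effect estimate at its primary time point

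*Protocol article*

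**What the plan says.** The section on GOSE at 6 months states: "The co-primary efficacy endpoint will be the Extended Glasgow Outcome Scale (GOSE) at 6 months after trauma". The Abstract and the Objectives section also list it among the primary endpoints.

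To hold the familywise error at 5%, the Statistical analysis section says "we will use a serial gatekeeping approach for statistical testing". The next sentence reads: "Analysis of GOSE at 6 months, as an ordinal outcome, will be done only if a significant difference in TIL is found". It is followed by: "The co-primary endpoint GOSE will not primarily be used to declare the study success". The same paragraph describes the output of the GOSE analysis: "The effect estimate will be an adjusted proportional odds ratio with 95% confidence interval". Nothing in the article says that this estimate will be reported when TIL is not significant.

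Other outcomes carry no such condition. Under Secondary endpoints: "Additionally, the GOSE will be assessed at discharge and 3 and 12 months follow-up". For secondary outcomes in general: "Secondary analyses will be compared between the treatment groups using unadjusted and adjusted (ordinal) logistic and linear regression". The subgroup paragraph plans forest plots for the primary outcomes, also without a condition.

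Reporting and dissemination says that "the results of the current trial will inform a phase III clinical trial", one powered on clinical outcome.

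**The concern.** Serial gatekeeping limits which hypothesis tests may support a claim. It does not require an estimate to be withheld, because an odds ratio with an interval that is presented descriptively uses no alpha. Here the condition falls on the analysis, and the odds ratio and interval appear only as products of that analysis.

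What is at stake is the treatment-effect estimate for a named co-primary endpoint at its primary time point. It would be missing when TIL, chosen to reflect the drug's mechanism, fails to show a difference. In that case anyone deciding on a phase III trial of clinical outcome would most want the 6-month functional estimate, whatever its width.

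**Working it through.** **Inputs, all from the Sample size section.** TIL difference 2.2, SD 3.2, two-sided alpha 0.05, power 90%, 53 per arm, about 10% loss.

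**Step 1: reproduce the plan's sample size.**
- Normal approximation: n per arm = 2 × (1.960 + 1.282)² × 3.2² / 2.2² = 2 × 10.51 × 10.24 / 4.84 = 44.5, so 45. Dividing by 0.9 gives 50 per arm, 100 in total.
- t-test: 45.4, so 46 per arm. 46 / 0.9 = 51.1, so 52 per arm, 104 in total.
- Rank test (relative efficiency 0.955): 46 / 0.955 / 0.9 = 53.5 per arm, 107 to 108 in total.

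The stated 106 lies between the last two, so the design inputs can be used as they stand.

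**Step 2: chance that the gate stays closed.** This is 1 minus the power of the TIL comparison. The standard error is 3.2 × √(2/n): 0.622 with 53 per arm and 0.660 with 47 (53 × 0.9 = 47.7, rounded down). For a difference of 2.2 and 53 per arm, the normal approximation gives power Φ(2.2/0.622 − 1.96) = Φ(1.58) = 0.943; the t-test gives 0.939. The t-test results are:

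| True TIL difference | 53 per arm | 47 per arm |
|---|---|---|
| 2.2 (planned) | 1 − 0.939 = 6% | 1 − 0.910 = 9% |
| 1.65 (assumed) | 1 − 0.749 = 25% | 1 − 0.696 = 30% |
| 1.1 (assumed) | 1 − 0.418 = 58% | 1 − 0.378 = 62% |
| 0 | 95% | 95% |

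At the nominal 90% power the first row would be 10%, which gives the range of 6–10% at the planned effect.

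**Step 3: what is reported if TIL is not significant, reading the text literally.**

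| Outcome | Status | Stated gate |
|---|---|---|
| GOSE at 6 months, overall | Co-primary | Yes |
| GOSE at discharge, 3 and 12 months | Secondary | None |
| Subgroup analyses on primary outcomes | Planned | None |
| Quality of life, all-cause mortality | Secondary | None |
| Complication rate | Primary (safety) | None |

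The secondary GOSE time points would be compared, and subgroup estimates of 6-month GOSE could be plotted, while the overall 6-month estimate is left out. The alternative is that the subgroup paragraph is also gated, which it does not say.

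**The case against.** The strongest reply is that the authors meant only the confirmatory test. The preceding sentence concerns statistical testing and familywise error, and the following one says GOSE is not the main basis for declaring success. Together the three sentences can be read as the order of tests, with loose use of the word analysis. The unconditional subgroup paragraph fits that reading. It may well be the intent, but the operative sentence does not say so, and no other sentence restores the estimate.

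Second, a reader might infer that the trial could end with no treatment-effect estimate on any patient-relevant outcome, or that harm behind an unchanged TIL could go unseen. The documents do not support either. GOSE at three other times, quality of life and all-cause mortality are ungated, complications are a primary safety endpoint in their own right, and the DSMB can advise stopping on adverse events, outcome and case fatality. GOSE at 6 months is also collected regardless, so the estimate could be recovered later, though it would then no longer follow the plan as written.

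Third, the co-primary label can be criticised, but the hierarchy is stated openly and relabelling would change no result. Gatekeeping the GOSE test is itself valid.

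**Conclusion.** The point holds for the 6-month time point. As written, the plan gives no adjusted odds ratio or 95% interval for a co-primary endpoint whenever TIL is not significant, and error control does not call for this. The probability is about 6–10% at the planned TIL effect, about 60% at half that effect and 95% with no effect.

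These figures rest on the plan's SD of 3.2 and an unadjusted t-test. The planned covariate adjustment could raise power and so lower the figures for non-zero effects. Differences below 2.2 are illustrative assumptions. No precision is given here for the GOSE odds ratio, because the article supplies no GOSE distribution from which to derive it.

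Sample size, familywise error, the TIL inference and data collection are unaffected. This is a free improvement of moderate priority.

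**What to change.** Replace the conditional sentence with wording such as: *The adjusted common odds ratio for GOSE at 6 months, with its 95% confidence interval, will always be estimated and reported. Its p-value supports a confirmatory claim only if TIL is significant at the two-sided 0.05 level; otherwise the result is descriptive.*

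State in the subgroup paragraph that its analyses of GOSE follow the same rule, so that overall and subgroup estimates appear together. Describing GOSE as second in the testing hierarchy would be clearer than co-primary, but this is optional.

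The cost is one or two sentences, settled before unblinding. N stays at 106 and the familywise error at 5%.
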